**Primary outcomes:**

Pulmonary function, Length of hospital stay.

**Second outcomes:**

Score of the Minnesota Living with Heart Failure Questionnaire (MLHFQ) in Portuguese version, Funcional capacity, The global perception of change scale, The functional independence measure (MIF), pO2 (partial pressure of oxygen), pCO2 (partial pressure of carbon dioxide), HCO3 (bicarbonate), Arterial Oxygen Saturation (SaO2), Base Excess (BE), Presence of lung complications.

**Other pre-specified outcomes:**

Duration of cardiopulmonary bypass, type of surgery, personal history, preoperative ejection fraction, previous respiratory complications, body mass index (BMI), gender and age.

**Trial registration:**

Trial register number NCT05966337.

## Introduction

Cardiovascular diseases are leading causes of both mortality and hospital admissions. Compared to other treatment modalities, cardiac surgery is distinguished by its advanced techniques and materials, which have led to safer procedures and reduced perioperative risks [1, 2].

In patients with cardiovascular diseases, including valvular disease, current guidelines advise considering exercise capacity for diagnosis and treatment planning [3, 4]. Moreover, coronary artery disease is the leading global cause of death, and patients undergoing coronary artery bypass surgery constitute a high-risk group [5]. Postoperative pulmonary dysfunction in patients undergoing cardiopulmonary bypass (CPB) is a significant clinical problem and has long been recognized by health professionals [6].

Postoperative pulmonary complications are highly prevalent, ranging from 5% to 20%, primarily due to perioperative factors and the intimate anatomical and functional relationship between the heart and lungs. These complications have been consistently associated with elevated postoperative morbidity and mortality rates [7, 8]. The etiology of pulmonary complications stems from a multifactorial process. Surgical factors like the use of cardiopulmonary bypass (CPB), anesthesia, surgical duration, mechanical ventilation duration, pleural opening, phrenic nerve alteration, use of mammary artery in myocardial revascularization surgery, sternal wound pain, and surgical drains lead to decreased functional residual capacity and increased intrapulmonary shunting. Furthermore, preoperative patient-related factors such as pre-existing lung diseases, smoking, advanced age, poor nutritional health, among others, predispose to complications [9].

Certain measures are employed during the postoperative period of cardiac surgeries to minimize pulmonary complications, including proper analgesia, oxygen therapy, and physiotherapy. Physiotherapy employs techniques such as deep breathing stimulation, cough stimulation, use of incentive spirometers, mobilization, and ambulation. However, at times these approaches fall short, and additional methods like Non-Invasive Ventilation (NIV) are employed [9].

Non-Invasive Positive Pressure Ventilation (NPPV) has been used to expedite pulmonary function recovery as well as to prevent and treat postoperative pulmonary complications [10]. NIV provides support for spontaneous ventilation. Its prophylactic use aims to reduce the incidence of endotracheal intubation, length of hospital stay, and prevent pulmonary complications. Non-invasive ventilation as a therapeutic resource was effective toward improving functionality; however, non-invasive ventilation did not influence the intensive care unit or hospitalization times of the studied cardiac patients [11]. Application of noninvasive ventilation (NIV), using face or nose masks has reduced the necessity of endotracheal intubation. It has been recognized that BiPAP/CPAP can prevent atelectasis and postoperative pneumonia, it also has beneficial effects in postoperative phase of cardiac surgery to prevent other pulmonary complications [12].

Postoperative pulmonary complications are the most common due to perioperative factors and the close anatomical and functional relationship between the heart and lungs. A prevalence of these complications ranging from 5% to 20% has been documented, and they are associated with increased postoperative morbidity and mortality [13].

Non-Invasive Ventilation (NIV) entails providing ventilatory support without utilizing an invasive artificial airway (endotracheal tube or tracheostomy tube). NIV aids breathing in patients with various conditions such as cardiogenic pulmonary edema, exacerbations of chronic obstructive pulmonary disease, and closed chest trauma. NIV improves gas exchange, assists in breathing, and reduces the need for intubation with positive pressure support. NIV diminishes the risk of ventilator-associated complications due to its non-invasive nature. As a result, NIV has been adopted to prevent complications in postoperative patients [10]. The use of NIV can be an important factor in patients undergoing cardiac surgery as part of a rehabilitation program and can also be a factor in reducing hospital stay, requiring larger studies to verify [14].

Continuous Positive Airway Pressure (CPAP) and Bilevel Positive Airway Pressure (BiPAP) are the most common methods of NIV^8^. Bilevel can be a successful tool for preventing the adverse effects of postoperative pulmonary complications after cardiac surgery [8].

Hence, in order to integrate these themes and provide further insight into the decision-making process for the optimal NIV modality in cardiac surgery patients, the objective of this research project is to conduct a randomized clinical trial and assess the efficacy of NIV in its CPAP and BiPAP modalities in comparison to conventional physiotherapy in terms of pulmonary function and clinical outcomes among patients undergoing cardiac surgery at a chosen hospital in Campina Grande, Paraíba, Brazil.

## Objectives

### Primary objective

Conducting a randomized clinical trial to assess the effectiveness of NIV in its CPAP and BiPAP modalities compared to conventional physiotherapy, in terms of pulmonary function and clinical outcomes among patients undergoing cardiac surgery at a selected hospital in Campina Grande, Paraíba, Brazil.

### Secondary objective

Describing the profile of cardiac patients undergoing cardiac surgery; outlining the patient profile concerning spirometry, Timed Up and Go (TUG) test, quality of life, The Global Perception of Change, vital signs, Functional Independence Measure (MIF), gasometric parameters, and pulmonary complications.

## Material and methods

### Type of study and location of research

The study protocol was conducted following the Standard Protocol Items: Recommendations for Interventional Trials (SPIRIT) checklist. This randomized, controlled, double-blind, parallel, three-arm clinical trial will take place at the João XXIII hospital, renowned for its expertise in cardiology and particularly cardiac surgery, serving a significant portion of the state and neighboring states. The hospital carries out an average of 8 cardiac surgeries weekly. The assessment and intervention will occur in both the ICU and the general ward.

The sample size was calculated using a 95% confidence level and 80% power, while considering the outcome of pulmonary function as a reference [13, 15]. Using the calculator on the openepi.com website, we arrived at a sample size of 63 patients. Recruitment will encompass both men and women aged 18 and above who have undergone cardiac surgery. Participants will be recruited through both spontaneous demand within the service and active search within the department’s records. The sampling method will be non-probabilistic convenience sampling.

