**Methods and analyses:**

This randomized, controlled, double-blind (patient and analyst) clinical trial will be conducted at Hospital João XXIII in Campina Grande, Paraíba, Brazil. Patients do not know which group they are allocated to. Those in the group that use CPAP or BIPAP will not be able to distinguish one from the other. The data analyst at the end of the collections will also be blinded. Only the health professional who will be applying the protocol cannot be blinded. The sample size, determined via sample calculation, yielded a total of 21 patients per group (63 patients). The patients will be allocated into 3 groups (CPAP group - CPAP + standard physiotherapy, BiPAP group - BiPAP + standard physiotherapy, and Control group - standard physiotherapy) in a 1:1:1 allocation ratio. The control group will receive the usual physiotherapeutic treatment as per the kinesiotherapy protocol. The treatment will be administered twice daily, starting in the ICU and progressing to the ward. In the CPAP group, nasal CPAP at 10cmH2O will be administered for 1 hour, twice daily, using an approved device. In the BiPAP group, nasal BiPAP with an IPAP of 13cmH2O and EPAP of 8cmH2O will be administered for 1 hour, twice daily, using an approved device. The NIV sessions will be conducted over the course of 5 days of hospitalization, both in the ICU and the ward. Assessments will be conducted at two time points: on day 1 preoperatively and on day 5 postoperatively. The following measures will be evaluated: pulmonary function, length of hospital stay, presence of postoperative pulmonary complications, score of the Minnesota Living with Heart Failure Questionnaire (MLHFQ) in its Portuguese version, functional capacity, the Global Perception of Change Scale, and the Functional Independence Measure (MIF). The normality of variables will be assessed using the Shapiro-Wilk test. IBM SPSS Statistics Base 25.0, using the Shapiro-Wilk test for normality and paired Student’s t-test for pre-post intervention comparison. They will use linear mixed effects models for longitudinal analysis and GLMMs to compare NIV effects over time between groups. They will employ ITT for missing data, INAR models for time dependence, fixed effects models for endogeneity, and Cohen’s d for effect sizes. Parametric model assumptions will be checked, and various models will be considered for data characteristics.

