### Post-randomization exclusion criteria

Undergoing hospital-based treatment contraindicating study participation (e.g., pacemaker implantation, pneumothorax requiring thoracic drainage).Death or other decompensations unrelated to the research.Return to the ICU.

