### Non-retention criteria

Patient not completing any of the follow-up evaluations.

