### Professional eligibility criteria

Hospital team physiotherapists.Physiotherapy students with prior training in the research protocol.

The sample will be randomized using the website www.randomization.com into three groups: participants will be divided into three groups (CPAP group - CPAP + usual physiotherapy care, BiPAP group - BiPAP + usual physiotherapy care, and control group - usual physiotherapy care), in a 1:1:1 allocation ratio for superiority. The groups will be coded, and the allocation will be concealed in consecutively numbered sealed and opaque envelopes. This study will involve three investigators: the first will be responsible for assessments; the second will manage the protocol application; and the third will oversee randomization.

This study protocol has received approval from the research ethics committee of Universidade Estadual da Paraíba, Brazil (CAAE: 65600722.1.0000.5187), and has been submitted to Clinical Trials (NCT05966337). Patient autonomy and anonymity will be respected, ensuring the privacy of personal data in accordance with Resolution No. 510/16 of the National Health Council and the Declaration of Helsinki. Before enrolling in the study, all patients will provide informed consent.

The study protocol was conducted following the Standard Protocol Items: Recommendations for Interventional Trials (SPIRIT) checklist [16].

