### Statistical analysis

The data will be analyzed using IBM SPSS Statistics Base 25.0 software for Windows. The normality of variables will be assessed using the Shapiro-Wilk test. The paired Student’s t-test will be utilized to compare data before and after the intervention. Linear Mixed Effects Models will be used for longitudinal data analysis. The effect of NIV (CPAP or BIPAP) combined with usual physiotherapy over time will be compared between groups using generalized linear mixed models (GLMMs), they can account for the correlation between repeated measurements within the same individual, which is important in longitudinal studies. The intention-to-treat (ITT) approach will be used to handle potential missing data. Time dependence is a key consideration in data analysis, and autoregression, particularly Integer Auto Regressive (INAR) models, is a valuable method for modeling this. However, selecting the appropriate autoregressive model is essential for gaining insights into the temporal dynamics of medical outcomes. Fixed effects models as a choice for addressing endogeneity. We use technique Bayesian model averaging to select relevant variables while controlling for overfitting. To ensure analysis accuracy, parametric model assumptions, such as homoscedasticity and residual normality, will be checked. Moreover, various models will be considered to accommodate specific data characteristics, such as skewness and zero-inflation/overdispersion.

Effect sizes will be calculated using Cohen’s d. Continuous variables will be reported as mean ± standard deviation (SD) along with a 95% confidence interval (CI), while categorical variables will be presented as absolute frequencies and percentages. The significance level will be set at 5% for all analyses (p ≤ 0.05).

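### 63 patients is given as the direct result of an 80%-power calculation with no stated allowance for loss, while the protocol excludes patients after randomisation

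*Protocol article*

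**What the plan says.** **Size.** Under Type of study and location of research the article says "The sample size was calculated using a 95% confidence level and 80% power", with pulmonary function as the sizing outcome and two citations. It continues: "Using the calculator on the openepi.com website, we arrived at a sample size of 63 patients". The Abstract says that the calculation "yielded a total of 21 patients per group (63 patients") and goes on to allocate the patients to three groups. The randomisation text gives the comparison as "in a 1:1:1 allocation ratio for superiority". The Statistical analysis section sets the test level: "The significance level will be set at 5% for all analyses (p ≤ 0.05"). No difference, SD, choice between FEV1 and FVC, expected loss or inflation step is given.

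**Removal of patients.** The Post-randomization exclusion criteria list a hospital treatment that rules out participation (pacemaker implantation and drained pneumothorax are the examples), "Death or other decompensations unrelated to the research", and return to the ICU. The Non-retention criteria add "Patient not completing any of the follow-up evaluations". Neither list comes with an expected rate.

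**Intention to treat.** The Concomitant care paragraph counts patients with a prolonged ICU stay on more advanced non-invasive ventilation, or a return to invasive ventilation, as non-adherent, and analyses them by intention to treat. The Statistical analysis section names intention to treat as the way missing data will be handled.

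**The concern.** The same number appears as the output of the power calculation and as the number to be allocated. Read plainly, that leaves no margin between patients randomised and patients who supply follow-up spirometry. The protocol itself names several ways for that gap to open in the days after cardiac surgery.

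Two things are at stake. First, a null result would be read as coming from a trial with 80% power, when the analysed number may support less. Second, the exclusions are tied to events related to outcome. Length of stay is a primary outcome and lung complications a secondary one. A patient who goes back to the ICU is likely to matter for both, and dropping such patients both shrinks the sample and selects it.

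**Working it through.** **1. Inputs.** From the article: 80% power, 5% significance level, 21 per arm, three arms, 1:1:1. Two-sided testing is assumed, because sidedness is not stated. Effect, SD and loss rate are not given.

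**2. The plan's own figure.** 63 cannot be reproduced without an effect and SD. The only route is to solve for the standardised difference d that makes 21 per arm give 80% power:

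- Normal approximation: d = (1.960 + 0.842) × √(2/21) = 0.865.
- Two-sample t-test (noncentral t, 40 df): d = 0.886.
- One-sided normal approximation: d = 0.767.
- Three-group ANOVA: f = 0.401.

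Each fits 21 per arm by construction, so none confirms or refutes the sponsor's calculation.

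**3. Power after loss.** For n evaluable per arm, power = P(|T| > t(0.975, 2n − 2)), where T is noncentral t with 2n − 2 df and noncentrality d√(n/2). At n = 19, for example, the noncentrality is 0.886 × √9.5 = 2.73, the critical value is 2.03 and power is 75.7%.

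| Evaluable per arm | Loss from 21 | t-test, d = 0.886 | Normal, d = 0.865 | Difference detectable at 80% (t-test) |
|---|---|---|---|---|
| 21 | 0% | 80.0% | 80.0% | 0.89 SD |
| 20 | 4.8% | 78.0% | 78.1% | 0.91 SD |
| 19 | 9.5% | 75.7% | 76.0% | 0.93 SD |
| 18 | 14.3% | 73.3% | 73.7% | 0.96 SD |
| 17 | 19.0% | 70.7% | 71.3% | 0.99 SD |

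The ANOVA version gives 75.4% at 19 per arm, 72.8% at 18 and 70.0% at 17. The three methods agree within about 1.3 points. One loss per arm costs about 2 points. Two per arm, 6 of 63, costs about 4.

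**4. Does intention to treat restore the loss?** Not for spirometry. There is one preoperative and one follow-up assessment, so a patient without the second adds little information on the treatment effect, whichever analysis set is named.

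**5. The rules side by side.** A patient who returns to the ICU and is re-ventilated meets the post-randomisation exclusion and also the Concomitant care rule. The first removes the patient; the second keeps the patient under intention to treat. Length of stay and complications are recorded during the admission and could still be available for such a patient.

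**The case against.** The strongest reply is that no stated figure has been shown to be wrong. The effect and SD rest on citations not reproduced in the article, and 0.886 SD fits only because it was forced to. A condensed article may leave the loss allowance to the full protocol. If 63 already held about 10% for loss, the requirement would be about 19 per arm (21 × 0.9 = 18.9) and no shortfall would follow at that loss. The loss rate is assumed too: follow-up is a few inpatient days, eligibility requires haemodynamic stability, and the Non-retention criteria define a category without forecasting its size.

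The t-test is also not the planned analysis, which uses mixed models. Suppose the sizing used the raw follow-up SD and the analysis adjusts for baseline. The effective difference is then d/√(1 − r²), with r the correlation between baseline and follow-up. At r = 0.5 power would be 86.6% with 19 per arm and 82.4% with 17; at r = 0.3, 79.6% and 74.7%. Neither r nor the sizing basis is documented.

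Most of this stands. A reader might infer that the 80% assumes complete follow-up on all 63, or that the design does not deliver 80% power. The documents support neither as fact: no sentence says that all 63 are taken as evaluable, and the true power cannot be computed. Nor does every serious course remove a patient, given the Concomitant care rule.

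The reply does not remove the ambiguity. The article says that the calculation yielded 63, which reads as raw output, and mentions no allowance. Under any of these analyses power still falls as evaluable patients are lost. The conflict between the exclusion list and intention to treat does not depend on the power figures at all.

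**Conclusion.** The point holds in conditional form. The article ties 80% power to 63 patients, allocates those patients, states no allowance and then excludes some after randomisation. If 21 per arm is the evaluable number required, any loss puts power below 80%. The illustrative size is about 76% to 71% for 19 to 17 evaluable per arm. That rests on four assumptions: a two-sided unadjusted t-test, a back-solved difference of 0.89 SD, equal loss across arms, and a loss of about 10% to 20% that has no source in the document. A loss of one per arm would be minor.

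Separately, and without any of these assumptions, the post-randomisation exclusions conflict with the intention-to-treat statements. As written they reduce the analysed sample on events related to the outcomes.

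**What to change.** 1. In the sample size paragraph, state that the 80% applies to 21 evaluable patients per arm, and say whether 63 is before or after an allowance for loss.
2. Give the effect and SD the sponsor actually used, and report power at the expected loss from those values. The back-solved 0.89 SD should not be written in as the target.
3. Reconcile the Post-randomization exclusion criteria with Concomitant care and Statistical analysis by keeping all randomised patients in the analysis. Whether a listed event ends the intervention is a separate matter; it should not remove data already available or still obtainable, including length of stay and complications. This cannot supply spirometry for patients who died.

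The cost is a few sentences and a stated power that may look less favourable. No extra enrolment is needed.

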### Inclusion criteria

Patients who have undergone cardiac surgery, aged 18 years or older, and are hemodynamically stable (controlled blood pressure, normal heart rate, conscious, oriented, and cooperative), with no medical restrictions for undergoing the treatment.

### Exclusion criteria

Presence of uncontrolled cardiac arrhythmias.Pre-existing neuromuscular disease.Vestibular symptoms.Orthopedic/musculoskeletal restrictions.Unstable angina.Stage 3 hypertension (resting systolic blood pressure ≥ 180 mmHg and/or diastolic blood pressure ≥ 110 mmHg).Resting heart rate > 120 bpm.Systemic hypotension with clinical impact (resting systolic blood pressure ≤ 90 mmHg and/or diastolic blood pressure ≤ 60 mmHg).Uncontrolled arrhythmias (Examples: complete atrioventricular block, second-degree type 2 atrioventricular block, atrial fibrillation, sustained ventricular tachycardia).Aortic dissection.

### Post-randomization exclusion criteria

Undergoing hospital-based treatment contraindicating study participation (e.g., pacemaker implantation, pneumothorax requiring thoracic drainage).Death or other decompensations unrelated to the research.Return to the ICU.

### Non-adherence to intervention criteria

Patient failing to complete 3 or more consecutive sessions.Patient voluntarily withdrawing from the study.Patient experiencing cardiac arrhythmia (atrial fibrillation, bradycardia) in two sessions despite medication and rest breaks.

### Non-retention criteria

Patient not completing any of the follow-up evaluations.

### Professional eligibility criteria

Hospital team physiotherapists.Physiotherapy students with prior training in the research protocol.

The sample will be randomized using the website www.randomization.com into three groups: participants will be divided into three groups (CPAP group - CPAP + usual physiotherapy care, BiPAP group - BiPAP + usual physiotherapy care, and control group - usual physiotherapy care), in a 1:1:1 allocation ratio for superiority. The groups will be coded, and the allocation will be concealed in consecutively numbered sealed and opaque envelopes. This study will involve three investigators: the first will be responsible for assessments; the second will manage the protocol application; and the third will oversee randomization.

This study protocol has received approval from the research ethics committee of Universidade Estadual da Paraíba, Brazil (CAAE: 65600722.1.0000.5187), and has been submitted to Clinical Trials (NCT05966337). Patient autonomy and anonymity will be respected, ensuring the privacy of personal data in accordance with Resolution No. 510/16 of the National Health Council and the Declaration of Helsinki. Before enrolling in the study, all patients will provide informed consent.

The study protocol was conducted following the Standard Protocol Items: Recommendations for Interventional Trials (SPIRIT) checklist [16].

